### 2.4. Study Population

The study population/sampling frame is composed of respondents at the household level who will be selected from two subcounties, one with mothers who have given birth between 2 and 12 months of age and who participated in the ttC model sessions (with 876 mothers in the treatment group forming part of the sampling frame), or mothers whose access to ttC sessions was limited to the other subcounty of interest (with 1355 mothers in the control group also forming part of the sampling frame). Thus, the total sampling frame/study population will have 2231 mothers from which the sample will be drawn. The mothers will be recruited from the CHW registers that show that they should have attended counselling sessions during their pregnancy. Inclusion criteria are that the mother had a baby between 2 and 12 months. All other mothers are excluded.

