### 2.5. Study Instruments

This study will use a cross-sectional primary data source. Structured household questionnaires will be administered to the study participants by the research assistants to gather quantitative data. The questionnaire includes different data types, such as categorical, numerical, and scale options, to facilitate the quantification of information. For validity and reliability, the questionnaire will have embedded skips and rules to ease data collection and perform real-time data cleaning. The study tools/instruments to be used will also include the village health team (CHWs) household registers that register all the mothers at the household level and the ttC register that includes the targeted sessions and number of visits. These will provide the contact and location from which participants will be sampled and the data collected retrospectively.

Tools will be uploaded to Kobo Kollect, a data collection application that will be loaded on phone devices and administered. The Kobo loaded questionnaire will also have mandatory questions marked for emphasis and will have an embedded translation into the local language to ease data collection. A field pretest of the structured questionnaire will be performed before the final roll out.

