### 2.8. Sampling Procedure

To reach the above calculated sample size, a three-stage sampling procedure will be used. First, a simple random sampling within Oyam district will be conducted to select one subcounty where the treatment (ttC implementation) was applied (Aber subcounty) and another where it was not (Otwal subcounty). This random selection ensured that both the intervention and the non-intervention areas were chosen in an unbiased manner.

In the second stage, stratified sampling will be done within the two subcounties to provide the sampling unit, being women of reproductive age (between 18 and 49 years) who have given birth to babies between 2 and 12 months of age. For internal homogeneity within each subcounty, two strata will be formed, one from each subcounty. A total of 930 mothers will be sampled from the 2231 eligible mothers (465 from the 876 available in the intervention subcounty and 465 from the 1355 available in the control subcounty) as per the sample size calculation above. 

Finally, in the third stage, a systematic sampling method will be applied to randomly select the 930 mothers from an alphabetically compiled list of eligible mothers. A random starting point and a fixed interval will be applied to select participants 465 participants from each subcounty. This process ensures an equal and unbiased representative sample for later generalisation of findings to other similar settings. The flow of this sampling process is shown in Figure 2 below.

By justifying and implementing this comprehensive sampling methodology, the study will aim to enhance the reliability and validity of the research findings.

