11th visit at 18 months of life (PNC)	Giving three to four meals to the child a day, child sleeping under a mosquito bed net.

Note: CHW = community health worker, ANC = antenatal care, HIV = human immunodeficiency virus, AIDS = acquired immunodeficiency syndrome, STIs = sexually transmitted infections, PoD = advised place of delivery, PNC = early postnatal care, ttC = timed and targeted counselling.

**Table 2 mps-07-00098-t002:** Study variables and their definitions.

Variable	Definition of Variable	Answering Scale
Intervention Variable		
ttC	This is a behavioural change approach implemented through CHWs to pregnancy households with a wide range of life-saving health practices through appropriately timed messages delivered using interactive storytelling to improve maternal health service utilisation. Mothers will be asked whether they received ttC from a CHW during their pregnancy.	1 = Yes 0 = No
Outcome Variables		
ANC	This is defined as visits to skilled health personnel during pregnancy. Mothers will be asked whether they attended any ANC visits during pregnancy.	1 = Yes 0 = No
PoD	This refers to the advised place of delivery, in a health facility. Mothers will be asked where they gave birth, with answering options including private health facilities, government health facilities, traditional birth attendant’s homes, or their own homes.	1 = Yes 0 = No
PNC	This refers to the care given mothers immediately after birth. This includes at least one PNC visit within the first 6 weeks after delivery. Mothers will be asked whether they visited a health facility for PNC after delivery.	1 = Yes 0 = No
Independent Variables		
Predisposing Factors		
Age	Mothers will be asked for their age at their last birthday.	1 = <20 2 = 21–25 3 = 26–30 4 = 31–35 5 = 36–40 6 = >40
Education level	Mothers will be asked for the highest level of school ever attended.	1. Preschool 2. Primary 3. O Level 4. A level 5. Tertiary 6. University 7. Non
Parity	Mothers will be asked how many births they have had in their lifetime, including the most recent one.	
Marital status	Mothers will be asked for their current marital status.	1. Widowed 2. Married or living together 3. Divorced or separated 4. Never married or never living together
Enabling Factors		
Income level	This refers to the income of the household. Mothers will be asked, on average, what is their approximate maximum monthly.	1. <200,000 2. >200,000–<500,000 3. >500,000–<1,000,000 4. >1,000,000–<2,000,000

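### Table 2's answer scales for age and income, two of the four matching covariates, leave values without a code, and Sections 2.4 and 2.8 give different maternal age rules

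*Protocol article*

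**What the plan says.** Table 2 of the protocol article gives a definition and an answering scale for each variable.

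- **Age.** The definition reads "Mothers will be asked for their age at their last birthday". The scale is "1 = <20 2 = 21–25 3 = 26–30 4 = 31–35 5 = 36–40 6 = >40".
- **Household income.** The definition reads "Mothers will be asked, on average, what is their approximate maximum monthly". The scale is "1. <200,000 2. >200,000–<500,000 3. >500,000–<1,000,000 4. >1,000,000–<2,000,000", and no further category follows.

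Sections 2.1 and 2.10 name education level, parity, income and age as the covariates. Section 2.10 puts them in a logistic regression to produce the propensity scores used for 1:1 matching.

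Eligibility is stated twice. Section 2.4: "Inclusion criteria are that the mother had a baby between 2 and 12 months. All other mothers are excluded". Section 2.8 describes the sampling unit as "women of reproductive age (between 18 and 49 years) who have given birth to babies between 2 and 12 months of age". Both sections use a frame of 876 mothers in the intervention subcounty and 1355 in the control subcounty, 2231 in all. Section 2.8 calls these mothers eligible.

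**The concern.** A coding scale should give every eligible respondent exactly one code. These two do not, and they belong to covariates that carry much of the adjustment. The groups are two non-randomised subcounties, and the Strengths and Limitations section relies on matching to deal with confounding. A covariate recorded inconsistently is balanced less well than the matched table will suggest. A covariate with no value gives that mother no propensity score unless the gap is handled in some way.

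The eligibility conflict concerns the target population. A mother of 17 with a baby of 6 months is included under Section 2.4 and excluded under Section 2.8. The sampling list, and the population to which the result applies, depend on which section is followed.

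**Working it through.** **Inputs.** Age and income scales: Table 2. Covariate list: Sections 2.1 and 2.10. Eligibility: Sections 2.4 and 2.8. Frame and sample: 876 + 1355 = 2231 and 465 + 465 = 930, which agree with the protocol's totals. The sample size calculation is not at issue here.

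**Step 1, age.** The printed codes were applied as literal rules to every whole age from 10 to 55, because age at last birthday is a whole number.

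| Age | Code |
|---|---|
| 19 or less | 1 |
| 20 | none |
| 21–25 | 2 |
| 26–30 | 3 |
| 31–35 | 4 |
| 36–40 | 5 |
| 41 or more | 6 |

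One age, 20, has no code. No age has two. A mother of 20 is eligible under both Section 2.4 and Section 2.8, so the gap lies inside the study population on either rule.

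**Step 2, income.** The four bands were applied in the same way to amounts from 0 to 3,000,000 in steps of 50,000.

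| Amount | Code |
|---|---|
| below 200,000 | 1 |
| exactly 200,000 | none |
| between 200,000 and 500,000 | 2 |
| exactly 500,000 | none |
| between 500,000 and 1,000,000 | 3 |
| exactly 1,000,000 | none |
| between 1,000,000 and 2,000,000 | 4 |
| 2,000,000 or more | none |

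The three interior gaps arise because neighbouring bands both exclude their shared boundary. The fourth arises because the scale has no open top category.

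**Step 3, number affected.** The protocol gives no distribution of age or income, so no estimate is possible. For scale only: 930 × 0.01 = 9.3 mothers for each 1% without a code. Assumed shares of 2%, 5% and 10% would be 18.6, 46.5 and 93 mothers. None of these shares comes from the protocol.

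**Step 4, eligibility.**

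| Mother with a baby aged 2–12 months | Section 2.4 | Section 2.8 |
|---|---|---|
| under 18 | included | excluded |
| 18 to 49 | included | included |
| over 49 | included | excluded |

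The counts of 876 and 1355 can be right under both rules only if no listed mother is under 18 or over 49. The protocol does not say so. Table 2 does not settle it, because its lowest and highest age bands are open-ended and fit either rule.

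**The case against.** The strongest reply is that Table 2 is a summary and not the form. Section 2.5 says the questionnaire mixes categorical, numerical and scale items, and age is asked as a number of years. If years are stored, the gap at 20 is a labelling slip that can be repaired at analysis with nothing lost. A field pretest is also planned and might expose a missing option. This stands as a limit on the harm. It does not remove the defect: the column gives the answering scale, nothing says that raw values are kept, and an income collected only in bands cannot be recovered later.

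Several stronger readings are tempting, and the protocol does not support them.

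- *Interviewers will be forced to miscode or lose the record.* Section 2.5 says only that the form "will also have mandatory questions marked for emphasis". It does not say that age or income is among them, and the form is not shown.
- *Many mothers are affected and power falls.* Requests for an approximate income may attract round figures, but that is inference. A power loss would further require every uncoded mother to be dropped, and the article states no complete-case rule.
- *The education codes are wrong.* No schooling is numbered 7, after University at 6. This does harm only if the codes enter the model as a numeric score, which the protocol does not say.
- *An age floor of 18 defeats the reason for choosing the area.* Section 2.2 mentions teenage pregnancy as added context. Its main reasons are where ttC is delivered, the shared district and the absence of a common border. Mothers of 18 and 19 remain eligible under Section 2.8.

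It can also be said that Section 2.4 is merely silent on age. It goes further: it gives one criterion and closes the list by excluding everyone else.

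**Conclusion.** The point holds as a defect in stated rules. Read as printed, Table 2 has no code for age 20, for incomes of exactly 200,000, 500,000 or 1,000,000, or for incomes of 2,000,000 and above. These are gaps in two of only four propensity covariates. Sections 2.4 and 2.8 disagree on maternal age while using the same frame counts.

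Confidence is high that the gaps and the conflict exist. The size of the effect is unknown. It depends on whether the form uses the printed bands or stores raw values, how many mothers fall on the gaps, and how missing covariates are handled. The first two are not stated, and the third may be set out in a fuller plan. If raw years are stored, the age gap costs nothing; the same holds for income stored as an amount. This should be corrected before fieldwork, but it does not by itself undermine the design.

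**What to change.** 1. Before the pretest, record age in completed years and income as an amount. If bands are kept, make them contiguous and exhaustive, for example ≤20, 21–25, 26–30, 31–35, 36–40, >40 for age, and <200,000; 200,000–499,999; 500,000–999,999; 1,000,000–1,999,999; ≥2,000,000 for income.
2. State that education enters the propensity model as categories and not as a numeric score, so that the order of its codes has no effect.
3. Reconcile Sections 2.4 and 2.8 to one maternal age rule, and confirm that 876 and 1355 were counted under it. If they were not, recount the frame before drawing the systematic sample.

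The first two are edits to the form and the text, and age is already asked in years. The third needs a check of the registers. An exact income may be harder for some respondents to give than a band; the exhaustive bands are then the alternative.

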### Conceptual Framework

The conceptual framework for this study is based on an adapted Andersen’s Behavioural Model (shown in Figure 1). It shows how maternal health behaviours are influenced by ttC in the presence of various factors proposed by Andersen’s model [25,26]. According to Andersen’s model, predisposing, enabling, and need-based factors affect maternal healthcare utilization [27]. In the current study, predisposing factors include social and demographic factors such as the mother’s age, education level, parity, and marital status. The enabling factors include income level of the household and male involvement in the pregnancy journey. The need-based factors are the presence of chronic illnesses, and psychological issues of the mother. While of importance to the study is the impact of ttC on maternal health behaviours, Andersen’s model helps us to account for how predisposing factors, enabling factors, and need-based factors shape healthcare utilisation. Secondarily, it contributes to understanding the contextual factors influencing maternal health outcomes, which supports efforts to address healthcare access inequality and inform policy development for more equitable access to care [25,26]. 

In this study, we shall incorporate Andersen’s model in investigating the impact of ttC (as an intervention) on ANC utilisation, PoD, and PNC. The ttC is hypothesised to influence maternal healthcare utilisation across the above three aspects by improving mothers’ knowledge on the benefits of fast and sufficient ANC visits, thus improving their attitudes towards ANC. ttC is also hypothesized to improve male-involvement, as well as enhancing the mother’s awareness of their health status and history, thereby affecting PoD and creating need for PNC.

**
General Objective
**

The main objective of this study will be to assess the impact of ttC on the maternal health continuum of care outcomes in Northern Uganda.

**
Specific Objectives
**

To investigate the impact of ttC on ANC utilisation among pregnant mothers.To evaluate the impact of ttC on the advised place of delivery among pregnant women.To assess the impact of ttC on PNC utilisation among mothers.

**
Hypotheses
**

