### 2.10. Data Analysis

After the data have been cleaned, they will be exported to STATA for analysis and Excel for better visualization. Descriptive and summary statistics will be drawn using the frequencies, measures of central tendency, and dispersion with proportions to provide a descriptive analysis of the context.

There will be cross tabulation of the chosen covariates (education level, birth parity, income, and age) with the intervention (ttC) to obtain their frequency distribution among the treatment and control arms together with the p-values. A logistic regression of the intervention and the covariates will be used to generate the propensity scores. A caliper width at the 20% of the standard deviation will be used for matching participants using the greedy nearest neighbor method in order to get the average treatment effects and the impact of the ttC intervention on the outcomes ANC, PoD, and PNC [40,41].

**
Sensitivity Analysis
**

Sensitivity analysis will be performed using the Rosenbaum bounds to test the conditional on the unobserved variables, and that the study is free from hidden bias [42]. This will use the rbounds commands in STATA version 14 ranging from 1 to 1.5 with an increment of 0.05. The gamma value will show whether hidden bias is present, as well as the robustness of the results to this potential hidden bias [43]. The sensitivity analysis results for the outcomes will demonstrate whether the treatment effects remain significant and robust to unobserved confounding, even in the presence of hidden bias. This should be across different gamma levels and confidence intervals to ensure the reliability and validity of treatment effects, therefore indicating stability [42,43].

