## 3. Discussion

This study protocol describes how the current study will evaluate the impact of the ttC model on the maternal health continuum of care outcomes in Northern Uganda using a cross-sectional quasi-experimental design and employing propensity score matching to control for selection bias [39]. This study will integrate Andersen’s behavioural model, which identifies predisposing, enabling and need-based factors, to obtain a comprehensive understanding of whether emphasizing these factors within the ttC model will result in a more effective maternal health continuum of care outcomes [26]. 

We expect that ttC will significantly improve the maternal health continuum of care outcomes ANC, PoD, and PNC. These outcomes are important to study because they have shown to improve the overall health and wellbeing of both the mother and the child, which reduces the infant and maternal mortality rates globally, thereby contributing to the achievement of Sustainable Development Goal 3 on health and well being [44,45]. Improved ANC utilisation has been linked to early identification of complications, and preventing maternal deaths and comorbid conditions like anaemia [45,46,47]. Ensuring that more women deliver at the advised PoD allows trained professionals to manage both anticipated and unanticipated complications that arise during delivery thereby preventing stillbirths and improving the survival rate of the newborns [48,49]. In addition, since the first days after birth are associated with the highest risks for both the mother and the baby, having PNC visits is essential for the prevention of infection and management of infectious diseases such as HIV and malaria, and maternal anaemia [50,51,52].

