**Figure 2 mps-07-00098-f002:**
[figure not shown]
The flow recruitment diagram.

**Table 1 mps-07-00098-t001:** The overview of key components of the ttC approach.

Timing (Outcome Focused On)	Targeted Counselling Given by CHW
1st visit between 2 and 3 months of pregnancy (ANC)	This should be as soon as possible when the mother misses their period so as to encourage the pregnant woman to go for ANC within the first trimester and identify the home care variability in the household that might be needed by the pregnant woman. The CHWs encourage male caregivers to accompany the women for ANCs. They encourage proper nutrition in pregnancy, uptake of iron/folic acid supplements, one extra meal a day for the pregnant woman, handwashing with soap, and having four or more ANCs.
2nd visit between 4 and 5 months of pregnancy (ANC)	This visit occurs at the middle of the pregnancy and is mainly focused on the disease burden, especially on HIV and AIDS, tuberculosis, and other STI testing and prevention awareness.
3rd visit between 6 and 7 months of pregnancy (ANC, PoD)	This visit is meant to promote delivery at a health facility, assisting the family in drawing up a birth plan, including having skilled personnel available during birth, and talk about available family planning measures to encourage 2-year period child spacing.
4th visit between 8 and 9 months of pregnancy (ANC, PoD)	This is one month before delivery to review the birth plan and reiterate the importance of essential newborn care practices. CHW also encourages exclusive breastfeeding and timely seeking for danger signs.
5th visit during the 1st week of life postnatal (PNC)	CHW encourages essential maternal and neonatal care, access to postnatal and postpartum care, and timely seeking for danger signs.
6th visit at 1 month postnatal (PNC)	Growth monitoring, encouraging vaccination against preventable diseases, and care seeking in case of fever.
7th visit at the 5th month of life (PNC)	CHW encourages complementary feeding and the importance of a balanced diet for the baby between the 6th and 9th months.
8th visit at the 9th month of life (PNC)	CHW encourages breast feeding along with complementary foods between the 9th and 12th months, and encourages uptake of micronutrients such as vitamin A supplements.
10th visit at the 12th month of life (PNC)	Encouraging iron rich foods, vitamin A supplements, deworming, and holistic child development.

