Male involvement	This is defined by male caregivers actively supporting their families and caring for their women in order to access better health services. The mothers will be asked whether their partner ever accompanied them to any ANC visits.	1 = Yes 0 = No
Need-based factors		
Presence of chronic illnesses	The mothers will be asked whether they have any chronic health conditions or illnesses (such as diabetes, cancer, HIV/AIDS, kidney/heart disease).	1 = Yes 0 = No
Psychological issues	Mothers will be asked whether they experienced any psychological problems during pregnancy (for example anxiety, depression, stress, body image issues).	1 = Yes 0 = No

Note: ANC = antenatal care, PNC = postnatal care, ttC = timed and targeted counselling, CHW = community health worker, PoD = advised place of delivery, HIV/AIDS = human immunodeficiency virus/acquired immunodeficiency syndrome.

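### Male involvement is measured only by partner attendance at ANC, so it is nested in the ANC outcome; it is also downstream of ttC, and should be kept out of the ttC-effect models

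*Protocol article*

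**What the plan says.** Table 2 (Section 2.9) places male involvement under Independent Variables, among the enabling factors. The row defines it broadly, as a man's active support and care, but one yes/no item measures it: "The mothers will be asked whether their partner ever accompanied them to any ANC visits". In the same table the ANC outcome is also yes/no: "Mothers will be asked whether they attended any ANC visits during pregnancy".

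The Conceptual Framework gives the variable two roles:

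- Background factor: "The enabling factors include income level of the household and male involvement in the pregnancy journey", and "Andersen’s model helps us to account for how predisposing factors, enabling factors, and need-based factors shape healthcare utilisation".
- Consequence of the intervention: "ttC is also hypothesized to improve male-involvement", described as part of the route by which ttC affects PoD and PNC. Table 1 makes the measured behaviour a task of the first counselling visit: "The CHWs encourage male caregivers to accompany the women for ANCs".

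Sections 2.1 and 2.10 both name the matching covariates as education, parity, income and age. Male involvement is in neither list. The Abstract promises adjusted odds ratios after matching and does not name the adjustment variables. The Discussion says that the framework factors will be used to learn "whether emphasizing these factors within the ttC model will result in a more effective maternal health continuum of care outcomes".

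**The concern.** There are two separate problems, and both lie in what the protocol states.

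First, the measure is nested in an outcome. Nobody can be accompanied to an ANC visit that did not take place. Every mother with male involvement = 1 has ANC = 1, so the data would show that involved partners go with ANC use whether or not partners influence it. A rise in this item under ttC also cannot be told apart from a rise in ANC attendance. This weakens the conclusions on enabling factors that the Conceptual Framework and the Discussion promise, whatever regression model is chosen.

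Second, a variable that ttC is designed to change is labelled an independent variable beside income and education. If an analyst takes the label at face value and adjusts for it, the ttC odds ratio for ANC is pulled down, and part of the PoD and PNC effects that the study wants to measure is adjusted away. The better ttC works with men, the more of its effect is hidden.

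**Working it through.** The plan gives no figure on this point. Its one design calculation, 465 per group, concerns facility delivery and reproduces: 2 × (1.96 + 0.842)² × 0.765 × 0.235 / 0.10² = 282.3; × 1.5 = 423.4; × 1.10 = 465.8. The point does not depend on it.

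**Inputs.** From the protocol: both variables are yes/no, male involvement = 1 implies ANC = 1, and ttC is expected to raise male involvement. The protocol gives no accompaniment rate, and no any-ANC rate by arm. The rates below are therefore assumptions, shown as a range.

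**Formula.** In one arm let a be the share with any ANC and m the accompanied share of ANC attendees, with non-attenders coded 0. In a logistic model for ANC that contains ttC and male involvement:

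- Mothers with male involvement = 1 have 100% ANC in both arms. They carry no information on ttC. Male involvement predicts the outcome perfectly, and Stata's logit drops these mothers.
- Among the rest, the odds of ANC are a(1 − m)/(1 − a).
- The ratio between arms is therefore: adjusted OR = unadjusted OR × (1 − m_ttC)/(1 − m_control).

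This is exact when ttC and male involvement are the only terms.

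**Example, assumed a = 93% control and 96% ttC, m = 40% and 60%.**

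- Unadjusted: (0.96/0.04)/(0.93/0.07) = 24/13.29 = 1.81.
- Adjusted: (0.96 × 0.40/0.04)/(0.93 × 0.60/0.07) = 9.60/7.97 = 1.20.
- Factor: 0.40/0.60 = 0.67.
- Mothers dropped: 0.93 × 0.40 = 37% of controls and 0.96 × 0.60 = 58% of the ttC group.

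With m = 40% and 50% the factor is 0.50/0.60 = 0.83.

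**Range, assumed m_control = 30%.**

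| m_ttC | Factor | ANC 90% vs 90% (unadjusted OR 1.00) | ANC 90% vs 95% (unadjusted OR 2.11) |
|---|---|---|---|
| 30% | 1.00 | 1.00 | 2.11 |
| 40% | 0.86 | 0.86 | 1.81 |
| 50% | 0.71 | 0.71 | 1.51 |
| 60% | 0.57 | 0.57 | 1.21 |

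Simulated data with a logistic fit gave 0.71 and 1.51 for the 50% row, as the formula predicts. If ttC does not change accompaniment there is no distortion. If ttC raises it, the odds ratio is biased downward, and a true null looks like harm.

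**If non-attenders are skipped and left missing.** Every mother with a recorded value then has ANC = 1, so an ANC model adjusted for the item has no variation in its outcome and cannot be fitted.

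**PoD and PNC.** Perfect prediction does not arise here. The issue is adjustment for a variable on the path from ttC to the outcome. The documents give nothing from which to size it.

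**The case against.** A reader might infer that the protocol's ttC effect is distorted by this variable. The documents do not support that. Section 2.10 takes the treatment effects from a match on a propensity score, and opens with: "There will be cross tabulation of the chosen covariates (education level, birth parity, income, and age) with the intervention (ttC". Section 2.1 gives the same four characteristics. Male involvement is in neither place, so the matched estimate is untouched. A place in Table 2 does not establish adjustment either: marital status, chronic illness and psychological issues stand under the same heading and are also absent from the score. An article may leave the post-matching adjustment set to a fuller document, so its absence is not held against the plan here. All of this stands, and it makes the distortion conditional.

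Three further objections also stand in part:

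- Male involvement is not one of the three listed hypotheses. The Conceptual Framework mentions it as a mechanism, and no analysis of it against ANC is set out. The Discussion's aim for the framework factors is general, but it does cover enabling factors.
- Section 2.5 mentions embedded skips, so non-attenders may be missing and not coded 0. That changes the form of the problem, as shown in the working, but does not remove it.
- The item directly measures a stated target of the first ttC visit, which is a good reason to keep it. It is not a reason to treat it as a background factor or as the sole measure of male involvement.

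What the objection does not reach is the wording of the item and the two roles given to it. Both are stated in the protocol. A later analysis plan could leave the variable out of a model, but could not recover an answer to a question that was never asked.

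**Conclusion.** The point holds in a limited form. Two parts rest on the text alone: the item is nested in the ANC outcome, and the protocol treats male involvement both as an independent enabling factor and as something ttC changes. Together they make the planned conclusions about this enabling factor unreliable, above all for ANC.

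The effect on the ttC estimate is conditional. The propensity-score match is not affected. Distortion arises only if the variable enters the adjusted odds ratios of the Abstract, which the Table 2 label and the Conceptual Framework suggest but nowhere state. In that case the ANC odds ratio is multiplied by (1 − m_ttC)/(1 − m_control), which runs from 0.57 to 0.86 across the assumed rates at which ttC raises accompaniment. The formula and its direction are firm. The sizes depend on assumed accompaniment rates and on non-attenders being coded 0. The change is worth making before data collection because it costs so little.

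**What to change.** - **Table 2.** Relabel male involvement as a mediator or descriptive variable, and state that it enters neither the propensity score nor the adjusted odds ratios for the ttC effect.
- **Questionnaire, before the field pretest.** Keep the accompaniment item. Add one item on partner support that requires neither ANC attendance nor facility delivery, for example support with household costs or decisions during pregnancy. Use it for any analysis of male involvement against ANC. Items on accompanying her to the delivery or on transport should be avoided, since they would repeat the nesting with PoD. The new item would still be open to influence from ttC, so it too stays out of the ttC-effect models.
- **Reporting.** Give ANC accompaniment descriptively, with the number of ANC attendees shown. It should not be presented as a between-group effect among attendees, because attendance is itself an outcome that ttC aims to change.

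The cost is one extra question, a changed label and a sentence. The small downside is less comparability with studies that use ANC accompaniment alone.
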